 **Date: 10 Nov 2010**

**Site:** Wolfson Institute of Preventive Medicine, Barts and the London School of Medicine, Queen Mary & Westfield College, University of London

| **TITLE** | **Investigation of Text Reminders on Adherence to Cardiac Treatment** |
| --- | --- |
| **SHORT TITLE** | INTERACT Study |
| **Protocol Version Number and Date** | Version 3 [ May 01 2012] |
| **Methodology** | Randomised controlled trial |
| **Study Duration** | 18 months |
| **Co-ordinating Centre** | **Wolfson Institute of Preventive Medicine** |
| **Objectives** | To assess the effect of programmed text message reminders on adherence to cardiovascular disease preventive medication. |
| **Number of Subjects/Patients** | 300 |
| **Main Inclusion Criteria** | Patients prescribed lipid lowering and/or blood pressure lowering medication. |
| **Intervention** | “Text Message Programme (TMP)”: periodic text messages, adapted in frequency to the responses received coupled with telephone or clinic consultation to resolve non-adherence. |
| **Outcome Measures** | **Primary**: Non-adherence to combination therapy  **Secondary**: serum cholesterol, blood pressure and cost-effectiveness |
| **Statistical Methodology and Analysis** | To estimate the absolute and relative differences (and 95% confidence intervals) in non-adherence to preventive therapy in the intervention and control arms, 6 months after enrolment in the study. Based on 30% non-adherence rate in the control arm and a 20% loss-to-follow up, a study of 300 participants has 80% power to detect a 50% reduction in non-adherence from TMP at the 5% level of significance. |

**Appendix E Text 23**

**Appendix F Letter 24**

**1. INTRODUCTION**

***1.1 Abstract***

A randomised controlled trial of text message reminders will be conducted in 300 patients who are receiving combination therapy with at least one lipid lowering drug (eg. a statin) and/or one blood pressure lowering drug (eg. an ACE-inhibitor). The intervention arm will consist of a “Text Message Programme” – periodic text messages asking whether patients have taken their medication, adapted, over time in their frequency, to the responses received, coupled with telephone or clinic follow-up to resolve reasons for non-adherence. The control group will receive standard care. Non-adherence to therapy (discontinuing one or more of the starting combination) will be assessed at 6 months by questionnaire. Serum cholesterol and blood pressure measurement will be undertaken as independent, objective measures of drug use. Allowing for a 20% loss-to follow up, the study has 80% power to identify a statistically significant reduction in non-adherence of 50% in the intervention group at a 0.05 level of statistical significance.

***1.2 Background***

Coronary heart disease (CHD) is the leading cause of death in both developed and developing countries.1 Approximately one third of all deaths are due to CHD in England and Wales.2

Combination drug therapy with antiplatelet, blood pressure and serum cholesterol lowering drugs is effective in reducing the risk of first cardiovascular disease events; about ¾ of all heart attacks and strokes could be prevented with complete adherence to treatment.

Non-adherence to medications is however common for patients with cardiovascular diseases and greatly reduces the preventive effect. Jackevicius and colleagues found that about one quarter of all patients with a history of myocardial infarction stopped their cardiac medications within 1 week of discharge from hospital3 and more than half had discontinued statin therapy two years later.4 Newby and colleagues found that less than half of patients with angiographically confirmed coronary artery disease remained on statins one year after starting treatment in hospital (44% non-adherence) and 79% of patients who had been prescribed the three required classes of preventive therapy (antiplatelet therapy, lipid lowering therapy and blood pressure lowering therapy) stopped at least one class of drug after one year.5 The levels of non-adherence may be under-estimated in these studies, based as they were on prescription re-fills and self-reported continuation on treatment, rather than objective measures (blood or urine tests) of drug intake.

Non-adherence to medical treatment is also a major health-economic problem. An estimated £100 million is wasted each year in Britain because of unused prescribed medications6. Reasons for non-adherence include side-effects of treatment, a belief that treatment is not-required, not remembering to take treatment, loss of interest in prevention when treatment has no perceptible benefit, and loss of contact with the prescribing medical team over time7. A recent publication from the National Institute for Health and Clinical Excellence called for interventions to improve the extent to which patients remain on effective medication for chronic conditions such as coronary heart disease8, which cost the NHS about £500 million in 2009.9 Non-adherence to cardiovascular medication therefore has a personal and economic impact.

Mobile telephone technology is increasingly used in clinical practice to improve contact with patients. Text message reminders are used to remind patients of clinic appointments10 and the need to attend for immunisation11. Text messaging has also been used to report blood pressure readings, blood results in patients with HIV and alter dose of medication in patients with epilepsy receiving anti-convulsant therapy12. The use of text messaging lends itself to improving adherence to take long-term medication, both by helping to establish a routine through text message reminders and also by identifying and correcting the causes of non-adherence as they arise. There is however a lack of randomised trial evidence demonstrating medical and cost-effectiveness of this approach. One randomised study on 70 participants in Australia evaluated the effectiveness of text message reminders on adherence to sunscreen application and showed a 92% increase in the use of sunscreen in the intervention arm13. There are no randomised studies of the use of text-message technology on adherence to cardiovascular preventive medication.

**2. Study Aims and Design of Proposed Investigation**

**2.1 Research Aim**

To conduct a randomised trial to assess the effect of a Text Message Programme (TMP) on non-adherence to combination cardiovascular disease preventive medication. The TMP involves sending text messages to patients, adapted in frequency to the responses received, to encourage medication adherence and to identify patients not-adhering to medication so that telephone or clinic-based assistance can be provided to resolve causes of non-adherence..

**The TMP is therefore, not only a means of reminding patients to take their medication, it is also a method for identifying those patients who, for whatever reason, have discontinued their treatment, so that medical assistance can be quickly offered to resolve the problem.**

**2.2 Study Objectives**

**Primary Objective**: to determine, in each randomised group, non-adherence to combined treatment with lipid lowering and/or blood pressure lowering treatment (Combination Therapy).

**Secondary Objectives**:

(i) Serum cholesterol and blood pressure levels at the end of follow up.

(iii) Cost-effectiveness of the Text Message Programme

***2.3 Study Design***

The study will be conducted in two parts:

Part 1: A pilot study on 30-50 patients to assess the feasibility of the text message protocol, the recruitment rate and therefore the number of recruiting centres required. Appendix A lists the questions that will be asked.

Part 2: Recruitment of a total of 300 patients.

The study will adopt a parallel group design

***2.4 Flow Diagram of Study***

Flow diagram based on:

**150**

Standard Care* alone

**150**

**45**

Text Messaging Program plus standard care*

**Non-adherence**

**23**

**6 month**

Self-reported adherence

Serum cholesterol and BP

**300 patients prescribed, lipid lowering and/or BP lowering treatment**

1. Non-adherence in control arm of 30% (ie 45 out of 150)
2. Expected 50% reduction in non-adherence by TMP
3. Loss to follow-up of 20%

*Standard care includes, hospital clinic review, General Practitioner consultations and community pharmacist review.

The figure bellow is indicative of the text message program protocol that will be adopted.

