***Follow-up Visit***

6 months from randomization, patients will be asked to return to attend a clinic follow-up visit. Each Patient will be asked questions to assess their adherence to lipid lowering and/or blood pressure lowering medication.

Other follow up measurements will include: Serum cholesterol, and blood pressure.

If a clear difference in non-adherence between the intervention and control arms is observed after 6 months, a further follow-up visit after 18 months, would be arranged to determine whether the effect of the TMP is sustained.

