**6. STATISTICAL CONSIDERATIONS**

***6.1 Number of Participants***

The TMP is expected to reduce non-adherence by 50%. Non-adherence among patients with angiographically confirmed coronary artery disease has been reported to be at least 50%3. To be conservative we have taken the non-adherence rate in the control arm to be 30%. A study of 300 participants would have 80% power to detect a 50% reduction in non-adherence at the 5% level of significance. This allows for a 20% loss-to-follow up.

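### The primary adherence outcome is collected only at the 6-month clinic visit, with 20% loss accepted and no route for patients who do not attend; the flow-diagram counts and one citation also need tidying.

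*Protocol*

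**What the plan says.** **Outcome collection.** At 6 months "patients will be asked to return to attend a clinic follow-up visit" (Section 2.4, Follow-up Visit), where adherence is asked about and cholesterol and blood pressure are measured. Section 4.5 lists the three questions: whether each drug class is still being taken, whether any days were missed in the past month, and how many. Both primary endpoints in Section 5.1 come from these answers. The schedule in Section 4.6 puts the questionnaire at follow-up only. Prescription refill is listed there too, but its footnote makes it an optional extra.

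**Contact during the trial.** Under Section 2.4 the TMP arm is texted daily, then on alternate days, then weekly. Patients who do not reply or who answer no are telephoned, and those who cannot be reached are sent a letter. The control arm has standard care. Section 4.3 records an address and mobile number for every participant.

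**Planning figures.** Section 6.1 states: "A study of 300 participants would have 80% power to detect a 50% reduction in non-adherence at the 5% level of significance", and adds: "This allows for a 20% loss-to-follow up". The synopsis agrees. The flow diagram lists the same 20% loss and gives "Non-adherence in control arm of 30% (ie 45 out of 150" for control, with 23 for TMP.

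**Source of the 30%.** Section 6.1 says "Non-adherence among patients with angiographically confirmed coronary artery disease has been reported to be at least 50%3" (the final 3 is the reference number), then "To be conservative we have taken the non-adherence rate in the control arm to be 30" per cent. Section 1.2 attributes the angiographic study to reference 5 and reports that "less than half of patients with angiographically confirmed coronary artery disease remained on statins one year after starting treatment in hospital (44% non-adherence" at that point. It also reports that 79% of patients prescribed three classes stopped at least one. It describes reference 3 as a post-infarction study in which about a quarter stopped within a week of discharge.

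**The concern.** The outcome needs only a few minutes of questioning, but as written it is obtained only from patients who come to the clinic. Non-attendance at a cardiovascular follow-up visit is plausibly related to not taking the medication, so the patients with no answer may not resemble those with one. The two arms also differ in how closely the study team stays in touch, so attendance may differ by arm. If both hold, the comparison of proportions among attenders is biased. An analysis plan can say how missing answers are treated, but it cannot supply answers that nobody asked for, so the collection rule belongs in the protocol.

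The smaller matters are of presentation. A diagram that lists 20% loss but counts events on all 150 per arm leaves the reader unsure which denominator is meant. A planning rate supported by a mismatched reference is harder to check.

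**Working it through.** **1. Inputs.** Control 30% (Section 6.1); halving gives 15%; 300 patients at 1:1 (Section 4.4), so 150 per arm; 20% loss (Section 6.1); 5% level. Two-sided testing is assumed, because sidedness is not stated.

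**2. The protocol's own figure.** Evaluable per arm: 150 × 0.80 = 120. With the usual two-proportion formula (pooled variance under the null, no continuity correction):

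power = Φ{[√n × |p1 − p2| − 1.96 × √(2p̄(1 − p̄))] / √(p1(1 − p1) + p2(1 − p2))}

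with p̄ = 0.225, √(2 × 0.225 × 0.775) = 0.5906 and √(0.21 + 0.1275) = 0.5809.

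At n = 120: (10.954 × 0.15 − 1.96 × 0.5906) / 0.5809 = 0.836, so power is 79.8%. The required size is 121 per arm, 242 in total, and 242 / 0.80 = 303 against the stated 300. The stated figure is reproduced.

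**3. Effect of less loss, same formula.**

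| Loss | Evaluable per arm | Power |
| --- | --- | --- |
| 20% | 120 | 79.8% |
| 10% | 135 | 84.3% |
| 0% | 150 | 87.9% |

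Expected non-attenders at 20% loss: 0.20 × 300 = 60.

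**4. Illustration of bias (assumed figures).** Suppose true non-adherence is 30% in both arms, 60% of lost patients are non-adherent, and one arm loses 25% and the other 15%.
- Arm losing 25%: (0.30 − 0.25 × 0.60) / 0.75 = 20.0% observed.
- Arm losing 15%: (0.30 − 0.15 × 0.60) / 0.85 = 24.7% observed.

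A spurious difference of 4.7 percentage points appears with no true effect. If controls are the ones lost more often, TMP looks worse. If TMP patients are lost more often, TMP looks better. With 20% lost in both arms, each shows (0.30 − 0.20 × 0.60) / 0.80 = 22.5% and there is no spurious difference.

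**5. Diagram counts.** 0.30 × 150 = 45 and 0.15 × 150 = 22.5, shown as 23: these are before loss. After 20% loss, 0.30 × 120 = 36 and 0.15 × 120 = 18.

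**6. Is 30% low relative to the cited evidence?** With non-adherence halved and 120 per arm:

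| Control rate | Where Section 1.2 or 6.1 gives it | Power |
| --- | --- | --- |
| 25% | reference 3, within 1 week of discharge | 70.1% |
| 44% | reference 5, statins at one year | 95.7% |
| 50% | lower bound stated in Section 6.1 | 98.3% |
| 79% | reference 5, at least one of three classes at one year | above 99.9% |

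The 30% is below every figure given for the angiographic population. Only the reference 3 figure is lower, and it concerns another population and a one-week horizon.

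**7. Section 1.2 against itself.** Fewer than half remaining on statins means more than 50% had stopped, yet the bracket gives 44% non-adherence. Both cannot describe the same measure.

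**The case against.** The case against has substance. The abstract speaks of a questionnaire, Section 4.5 says every patient will be questioned, contact details are held for all, and nothing says that non-attenders are excluded. Treatment of missing outcomes is commonly left to an analysis plan, which is not at hand. This limits the point: it is a cheap improvement to data collection, not an error in the analysis. It does not remove it, because the Follow-up Visit text and the schedule place the questions at the visit and name no fallback. The telephone-then-letter sequence in Section 2.4 belongs to the intervention, so controls do not receive it.

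The bias example rests on invented loss rates and an invented rate among the lost. That is correct; it shows the mechanism and not an expected size.

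Two stronger readings are tempting. A reader might infer from 45 and 23 of 150 that the planning figures conflict and the power is wrong. They do not: the synopsis, abstract and Section 6.1 agree, and the power reproduces at 120 per arm. The diagram makes no power claim. A reader might also infer that Section 1.2 contradicts the description of 30% as conservative. It does not: although 44% is below the 50% in Section 6.1, fewer than half remaining and 79% stopping at least one class both agree with it, and 30% lies below all of them. The 79% includes antiplatelets, and these figures are at one year while the trial measures at 6 months, so they are an imperfect guide, but they give no ground for deleting the word.

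**Conclusion.** The primary outcome should not depend on clinic attendance when three questions suffice. Providing another route is worth about 4.5 percentage points of power (79.8% to 84.3%) if it halves the loss, assuming 30% against 15% and a two-sided 5% test. It also limits attrition bias. The size and sign of that bias cannot be derived from the protocol; if the control arm loses more patients and the lost are less adherent, it works against TMP.

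A reader might go further and count all lost patients as non-adherent. That gives 0.20 + 0.80 × 0.30 = 44% against 0.20 + 0.80 × 0.15 = 32%, with 57% power at 150 per arm. The protocol proposes no such rule, so this is not a criticism of its stated power.

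The diagram counts, the reference in Section 6.1 and the statin sentence in Section 1.2 are minor editorial corrections. None changes the sample size of 300 or the 80% power.

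**What to change.** **Main change, Section 2.4, Follow-up Visit.** State that patients in either arm who do not attend will be sent the same adherence questions by post, or asked them by telephone with a fixed script, within a set window around 6 months, and that the mode of collection will be recorded.

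**Minor corrections.**
- Flow diagram: show 36/120 and 18/120, or label 45 and 23 as counts before loss to follow-up.
- Section 6.1: reconcile the reference 3 citation with Section 1.2, checking the figure against the source.
- Section 1.2: reconcile the proportion remaining on statins with the 44%, again from the source.

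**Cost.** Up to about 60 short contacts, a small difference between clinic and remote answers (which recording the mode allows to be examined), and some rewording. No extra patients are needed. Cholesterol and blood pressure would still be missing for patients who do not attend.

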***Text Message Program Algorithm***

**Randomisation**

Text message sent **DAILY**

Text message sent on

**ATERNATE DAYS**

Text message sent **WEEKLY**

Follow up visit

**Phase 1**

**Phase 2**

**Phase 3**

**Week 1-2**

**Week 3-4**

**Weeks 5+**

**End of study**

Patients receive a daily text message for the first 2 weeks of the study (*Phase 1*), every alternate day for the second 2 weeks of the study (*Phase 2*), and weekly thereafter (*Phase 3*).

The wording of the text messages will vary according to the phase of the TMP protocol. An example of the daily text massage reminder is:

‘***Hello Mr/Mrs……. Have you taken your heart medication today? Please text back “Y” if the answer is Yes, I took my medication before receiving this text”, “P” if the answer is “Yes, the message prompted me to take my medication” and “N” if the answer is “No”. Thank you. From The Barts and The London Heart Team***’.

Any non-responders or patients who reply back ‘NO’ in response to the message will receive a telephone call form the study coordinator, to determine whether the patient is experiencing problems taking their medication, and resolve this if possible (e.g. the patient has run out of medication or they have been abroad).

If specialist advice is needed (e.g. whether symptoms may be a side-effect of treatment) participants will be informed that they will be contacted by a study pharmacist or doctor within the next few days. If the problem can not be resolved over the phone the patient will be advised to make an appointment with their GP. A letter will be sent to the patient’s GP summarising the problem with their medication and a copy of this letter will be sent to the patient’s home address.

If patients can not be contacted by telephone, a letter will be sent to their home address informing them that we have been unable to contact them by telephone and asking them to contact the study team (Appendix B).

***Follow-up Visit***

6 months from randomization, patients will be asked to return to attend a clinic follow-up visit. Each Patient will be asked questions to assess their adherence to lipid lowering and/or blood pressure lowering medication.

Other follow up measurements will include: Serum cholesterol, and blood pressure.

If a clear difference in non-adherence between the intervention and control arms is observed after 6 months, a further follow-up visit after 18 months, would be arranged to determine whether the effect of the TMP is sustained.

**3. STUDY POPULATION**

***3.1 Inclusion Criteria***

Participants will be men and women of all ages who own a mobile phone with text message capability. Patients will be on a combination of medicines (at least a lipid lowering drug and/or a blood pressure lowering drug) for cardiovascular disease preventive treatment.

It is anticipated that most patients will be on both classes of drug (since these are recommended for cardiovascular disease prevention). However patients who for some reason are only on one class (eg. they may be intolerant of all blood pressure lowering drugs) will still be eligible and non-adherence to the one class will be assessed.

***3.2 Exclusion Criteria***

There are no exclusions

**STUDY PROCEDURES**

***4.1 Recruitment***

Participants will be recruited from angiography and cardiovascular disease prevention clinics (eg. cardiology, hypertension and diabetes clinics). Patients who are on appropriate cardiovascular preventive treatment will be approached by a study investigator in the clinic waiting area and given a study information leaflet. After patients have been seen by the doctor they will be seen again by the study investigator who will answer any questions they may have about the study and ask them if they would be willing to participate. Written consent will then be sought. Patients on appropriate treatment could also be identified by the clinical care team from a search of the practice database and sent a text message (Appendix E) or a letter (Appendix F) informing them of the study and asking them to contact the study team if they would like to find out more about the study. Interested participants would then be offered an appointment to meet a study investigator at their local general practice, to answer any questions they may have and ask them if they would be willing to participate. Written consent will then be sought.

***4.2 Consent***

All patients will be asked to give written consent prior to participation as described above.

***4.3. Data Collection***

When a person agrees to participate the following will be recorded: Participant’s name, age, gender, address, date of birth, mobile phone number, and GP details. Each participant will be allocated a unique study number.

Details of the participant’s medical history will be recorded including prior history of cardiovascular disease, diabetes, smoking and cardiovascular risk factors.

***4.4 Randomisation***

Participants will be randomly allocated to receive either the TMP (the intervention arm of the trial) or standard care (the control arm of the trial). Participants will be randomised after they have given consent to be in the trial, so that the decision to participate has no bearing on which arm of the trial they are allocated to. A random sequence will be generated by computer in blocks of 12 to ensure balanced 1:1 randomisation.

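### Section 4.4 fixes and prints a single block length of 12 in a trial that cannot be masked, so a fully informed recruiter could know up to one allocation in seven in advance

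*Protocol*

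**What the plan says.** Section 4.4 allocates participants 1:1 and describes the sequence as follows: "A random sequence will be generated by computer in blocks of 12 to ensure balanced 1:1 randomisation". It mentions no other block length. It does not say who holds the sequence, whether recruiters can see past allocations, or whether there is one list or one per clinic. The safeguard it offers is timing: "Participants will be randomised after they have given consent to be in the trial", so that joining the trial and the arm received stay unconnected.

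Section 4.1 gives recruitment to a study investigator. That person approaches treated patients in the waiting area, and after the consultation "they will be seen again by the study investigator who will answer any questions they may have about the study". The investigator then asks them to take part, and written consent follows. A second route runs through general practices: the clinical care team searches the database, patients who are interested contact the study team, and they are offered an appointment with an investigator. Section 3.2 lists no exclusions.

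The flow diagram in section 2.4 describes one arm as "Text Messaging Program plus standard care". For the other, section 1.1 says "The control group will receive standard care". In the text message algorithm, a patient who does not answer, or answers no, "will receive a telephone call form the study coordinator"; the GP letter in Appendix B gives the call to a study doctor or pharmacist. The primary endpoints in section 5.1 are continuation of therapy and days missed in the last month. Both come from questions put to the patient at the end of the study (section 4.5).

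**The concern.** With a fixed, published block length, the rest of a block is known as soon as one arm has used its six places. Masking would normally limit this, because recruiters would not know the earlier allocations. Here one arm receives text messages and calls and the other does not, so study staff can learn who is in which arm.

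Randomising after consent protects the patient's decision from knowledge of the arm. It does not protect the recruiter's earlier decisions about whom to approach, how firmly to encourage and when. With no exclusion criteria, those decisions are largely discretionary. If patients who seem motivated were approached when the text message arm was due, and others when control was due, the arms would differ in the trait that drives a self-reported adherence outcome. Motivation is not among the baseline items in section 4.3, so adjustment could not be relied on to remove the difference.

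**Working it through.** The protocol states no figure for predictability, so there is none to reproduce.

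**Inputs.** Block length 12 and ratio 1:1, so m = 6 places per arm (section 4.4). Total 300 (section 2.3), so 300/12 = 25 complete blocks. Planned non-adherence 30% in control, halved to 15% (section 6.1), a 15-point difference. The observer is assumed to know the block length, where each block starts and all earlier allocations in it.

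**1. Certain allocations per block.** There are C(12,6) = 924 equally likely blocks. At least the last k places are forced when they all belong to one arm, which happens in 2 × C(12 − k, 6) of them.

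| k | Blocks with at least k forced places | Share |
|---|---|---|
| 1 | 2 × 462 = 924 | 100% |
| 2 | 2 × 210 = 420 | 45% |
| 3 | 2 × 84 = 168 | 18% |
| 4 | 2 × 28 = 56 | 6.1% |
| 5 | 2 × 7 = 14 | 1.5% |
| 6 | 2 × 1 = 2 | 0.2% |

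The expected number is the sum of the shares: (924 + 420 + 168 + 56 + 14 + 2)/924 = 1584/924 = 1.714. This agrees with the closed form 2m/(m + 1) = 12/7 and with enumeration of all 924 blocks. As a share it is 1.714/12 = 1/7 = 14.3%. Over 25 completed blocks it is 25 × 12/7 = 42.9, about 43 of 300. Of these, 25 are simply the last place in each block.

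**2. Best guess.** Always guessing the arm that is behind gives [6 + (4096/924 − 1)/2]/12 = 7.716/12 = 64.3%, against 50% by chance.

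**3. Unfinished blocks.** No place can be forced before place 7. A clinic list that stops at or before place 6 of a block adds nothing from that block, and one that stops later adds less than a full block would. Separate lists that end mid-block therefore bring the total below 43.

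**4. Possible consequence (assumption).** Suppose every forced place were steered, and the patients steered to the two arms differed in underlying non-adherence by d points. The bias would be d/7. For d = 10 to 30, an assumed range, that is 10/7 = 1.4 to 30/7 = 4.3 points, against the planned 15.

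**5. Alternatives.** Shorter fixed blocks are worse: the share 1/(m + 1) is 20% for length 8, 25% for 6 and 33% for 4. For randomly varying lengths, 400 trials of 300 patients were simulated per set. The observer knew the set of sizes but not their order. The sets are illustrative.

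| Scheme | Certain allocations | Best guess correct |
|---|---|---|
| Fixed 12 (exact) | 14.3% | 64.3% |
| 8/10/12 | 1.3% | 65.1% |
| 8/12/16 | 1.6% | 64.0% |
| 4/6/8 | 2.1% | 68.1% |

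Of 300 patients, 1.3% is about 4 and 1.6% about 5. The simulation counts only strict certainty; predictions that are likely but not certain remain.

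**The case against.** The strongest case against is that one in seven describes an observer whom the protocol does not show to exist. Recruitment spans several kinds of clinic as well as general practices. The calls are made by a coordinator, a role not described as recruiting, and section 4.4 speaks of one sequence. Recruiters who see only part of a shared list know less. Who holds the list is operational detail that may sit in another document. Twelve is a comparatively long block, and among fixed lengths a fairly safe one. In 55% of blocks only the final place is ever certain. Even the 1.4 to 4.3 point bias requires complete knowledge and systematic steering.

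Most of this stands, and it limits the size of the point. The figure of 43 is a ceiling. It would also be wrong to say that exposure is unchanged if lists are kept by clinic, because unfinished blocks reduce it. Nor does section 4.1 show that the investigator controls the timing of practice-based appointments: those patients make contact themselves, and the text does not say who sets the date. Section 4.4 already places randomisation after consent, so that part is not missing.

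The 64% figure gives the remedy no support, since varying the lengths leaves it about the same and short blocks raise it.

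What the objection does not remove is that the protocol itself chose one length and printed it, and that its stated safeguard acts after the stage at which steering would happen.

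**Conclusion.** The point holds as a weakness in a stated design choice. Fixing and printing a block length of 12, where arms are visible and recruitment is discretionary, exposes up to one allocation in seven (at most about 43 of 300 in expectation) to certain prediction. That rests on a recruiter with full knowledge of one list made up of completed blocks; with less knowledge, or lists ending mid-block, the share is lower.

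A reader might infer that about 43 allocations will be known in advance, or that the comparison will be biased by selection. The documents support neither: they do not show that recruiters see past allocations, and nothing suggests that steering is expected. A reader might also infer that the protocol contains a wrong number. It does not.

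**What to change.** In section 4.4, replace the fixed length with a statement that block lengths vary at random, that the lengths and the sequence are withheld from staff who recruit, and that the lengths do not appear in the protocol. Add that an allocation is released only after baseline data, as well as consent, are recorded. The schedule in section 4.6 puts consent, medical history and blood pressure on the day of randomisation without fixing their order.

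Avoid sets with short blocks: 4/6/8 raises best-guess accuracy to 68%, whereas 8/10/12 or 8/12/16 keep it at 64 to 65% and bring certain allocations down to about 1 to 2%, even for an observer who knows the set.

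The cost is a small rewording of section 4.4 and a new computer list. The 25 fixed blocks would end in exact balance at 300. With varying lengths on one list, the last block may be incomplete, and the final difference between arms is then at most half the largest block: 6 patients for 8/10/12, or 8 for 8/12/16.
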